#### The Collabri Flex Trial for Anxiety

Clinically relevant treatment response is defined as a 4-point difference in anxiety symptoms measured with the BAI. The estimation is based on studies using the BDI [66, 67], because, to our knowledge, there are no comparable Danish studies using the BAI. Additionally, we could not find any Danish studies that could contribute to the estimation of the SD for the BAI in this population. Therefore, the SD is set to 12 based on international surveys [68–70]. Based on these figures, the sample size calculation shows that 284 individuals should be included in the anxiety trial to be able to reject the null hypothesis that the collaborative care group and the consultation liaison group have improved similarly in terms of anxiety symptoms with a power of 0.8 and a significance level of 0.05.

Power calculations for the secondary outcomes showed that 120 participants in each group in the depression trial and 142 participants in each group in the anxiety trial will be sufficient to detect relevant significant differences in the secondary outcomes with a power above 80% (see Tables 3 and 4). The power calculations were performed subsequent to the sample size calculations. Some of the figures are based on Collabri data that were not available at the time of sample size calculations.

**Table 3 Tab3:** Power calculations for secondary outcomes in the depression trial

	δ value for clinically relevant difference	α value for type I error	σ value for the within-group SD	Calculated power	Reference
BAI	4	0.05 (5%)	10	0.870 (87.0%)	[66, 67] SD is based on data from the Collabri depression trial (not published)
SDS	4	0.05 (5%)	9	0.930 (93.0%)	[51, 52, 71]
SCL-90-R	23	0.05 (5%)	50	0.944 (94.4%)	[72]
WHO-5	10	0.05 (5%)	18	0.990 (99.0%)	[55, 73] SD is based on data from the Collabri depression trial (not published)

*BAI* Beck Anxiety Inventory, *SCL-90-R* Symptom Checklist 90-Revised, *SD* standard deviation, *SDS* Sheehan Disability Scale, *WHO-5* World Health Organization-Five Well-being Index

**Table 4 Tab4:** Power calculation for secondary outcomes in the anxiety trial

	δ value for clinically relevant difference	α value for type I error	σ value for the within-group SD	Calculated power	Reference
BDI-II	4	0.05 (5%)	11	0.863 (86.3%)	[66–69]
SDS	4	0.05 (5%)	10	0.920 (92.0%)	[51, 52, 71]
SCL-90-R	23	0.05 (5%)	50	0.972 (97.2%)	[72]
WHO-5	10	0.05 (5%)	26	0.898 (89.8%)	[55, 73] SD is based on data from the Collabri anxiety trial (not published)

*BDI-II* Beck Depression Inventory II, *SCL-90-R* Symptom Checklist 90-Revised, *SD* standard deviation, *SDS* Sheehan Disability Scale, *WHO-5* World Health Organization-Five Well-being Index

### Statistical analyses

The null hypothesis tested in both trials is that there is no difference in depression and anxiety symptoms, respectively, between the two groups (collaborative care and consultation liaison) at 6 months’ follow-up. For continuous outcomes, including the primary outcomes, analysis of variance (ANCOVA) will be used to examine differences between group means. For exploratory binary outcomes, logistic regression analysis will be used to detect differences between groups. All analyses will be adjusted for stratification variables. The trials will be conducted according to the statistical principle “intention-to-treat”, which means that analyses will be based on all included participants. If necessary, multiple imputations will be used to address the issue of missing data.

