### Recruitment and randomization

The GP provides oral and written information about the study, obtains oral and written consent, and refers patients with depression or anxiety to the trials. A care manager contacts the patient to arrange a diagnostic eligibility interview assessing the inclusion and exclusion criteria. If the patient meets the inclusion criteria and is not excluded, a Collabri Flex team member performs the randomization through the Odense Patient data Explorative Network (OPEN), which is an external web-based randomization provider [28]. The allocation sequence is computer generated and the block sizes are variable. The randomization in both trials is stratified by former psychological and/or pharmacological treatment for anxiety or depression (yes/no). In the depression trial, an additional stratification variable is the degree of depression as assessed in the eligibility interview (mild/moderate/severe), and in the anxiety trial an additional stratification variable is the type of anxiety disorder assessed as the primary diagnosis (generalized anxiety disorder/panic disorder/social anxiety disorder). The care manager will contact the patient with information about the result of the randomization. If the patient is allocated to collaborative care, the care manager will schedule the first consultation. If the patient is allocated to the group offered consultation liaison, the GP will continue the treatment. Ideally, the time from referral to randomization should not exceed 3 weeks (see Table 1).

**Table 1 Tab1:** Standard Protocol Items: Recommendations for Interventional Trials (SPIRIT) figure: enrolment and data collection

	Baseline *t*_−1_ (0–3 weeks)	Randomization *t*_0_	6-month follow-up *t*_1_
Informed consent	x		
Eligibility interview	x		
Allocation		x	
Questionnaire data	x		x
Register data		x	x
Data on intervention activities		x	Continuous data collection throughout the intervention

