### Data collection and data management

Data will consist of information obtained by the Collabri Flex team (from baseline throughout the study period), self-reported questionnaire data and register data.

The baseline diagnostic eligibility interview is supervised by and delegated by the psychiatrist. The diagnostic assessment is based on the Mini International Neuropsychiatric Interview (MINI) [40], in which all care managers have received extensive training. The psychiatrist is always consulted to discuss the assessment and clinical impression. If there is disagreement between the result of the diagnostic assessment and the GP’s referral diagnosis, the psychiatrist contacts the GP to agree on the primary diagnosis and potential secondary diagnoses. In connection with the diagnostic assessment, the care manager obtains additional baseline information using the Standardized Assessment of Personality Abbreviated Scale (SAPAS) [41] and, if relevant, the Attention-Deficit/Hyperactivity Disorder Symptom Checklist for Adults (Adult ADHD Self-report Scale (ASRS)) [42]. Self-reported questionnaires will be completed electronically before the diagnostic assessment and 6 months after randomization.

Diagnostic assessment data, intervention-specific data and self-reported questionnaire data are collected through and stored in the electronic system REDCap [43], which is the data management system required by the Capital Region of Denmark. Other data, such as data extractions for quality assurance, are stored in entry-restricted files on secured and logged servers. Blinding will be maintained.

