### Sample size and power calculations

#### The Collabri Flex Trial for Depression

Clinically relevant treatment response at group level is defined as a 4-point difference in depression symptoms measured by the BDI-II [66, 67]. At the time of sample size calculation, we found no relevant Danish studies that could contribute to the estimation of the within-group standard deviation (SD) for the BDI-II in this population. Therefore, the SD for the BDI-II is set to 11, based on international surveys [66–68]. A sample size calculation based on these figures shows that 240 participants should be included to be able to reject the null hypothesis that the collaborative care group and the consultation liaison group have improved similarly in terms of symptoms with a power of 0.8 and a significance level of 0.05.

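### The adjustment stated for the primary ANCOVA names the stratification variables but not the baseline BDI-II or BAI score; the model is left unclear and, read literally, gives up precision, mostly in the anxiety trial

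*Protocol article*

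**What the plan says.** The Statistical analyses section of the protocol article gives the model and the adjustment:

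- Model: "For continuous outcomes, including the primary outcomes, analysis of variance (ANCOVA) will be used to examine differences between group means".
- Adjustment: "All analyses will be adjusted for stratification variables".

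Recruitment and randomization lists the stratification variables. Both trials use former treatment (yes or no). The depression trial adds a three-grade severity rating from the eligibility interview. For the other trial, "in the anxiety trial an additional stratification variable is the type of anxiety disorder assessed as the primary diagnosis". Every one of these is categorical.

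The baseline scores are planned. Data collection and data management says: "Self-reported questionnaires will be completed electronically before the diagnostic assessment and 6 months after randomization". Table 2 marks BDI-II, BAI, SDS, SCL-90-R and WHO-5 at both baseline and 6 months, in both trials. The baseline value of the outcome is not mentioned anywhere in Statistical analyses, either as a covariate or as something left out.

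**The concern.** An analyst who follows the section as written fits treatment plus categorical strata and nothing else. That is in effect an analysis of variance, although the abbreviation given is ANCOVA. The text therefore supports two different primary models, with and without the continuous baseline score.

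The choice affects precision. The baseline score usually predicts the follow-up score well. Leaving it out widens the confidence interval and lets a chance difference in baseline scores carry through to the estimate. The anxiety trial is more exposed, because neither of its stratification variables measures how severe the symptoms are. The depression trial has a coarse severity grade that does part of the work. If the covariate set stays open, it could also be settled after data have been seen. The coded groups described under Blinding reduce that risk but do not replace naming the model in advance.

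**Working it through.** **Inputs from the article (Sample size and power calculations).** Target difference 4 points in both trials; SD 11 (BDI-II) and 12 (BAI); power 0.80; significance level 0.05; 120 per group (240) and 142 per group (284). Sidedness is not stated. One-sided testing would give 188 and 224 in total, so the plan's figures are two-sided.

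**Step 1: reproduce the plan's figures.** n per group = 2 × (1.960 + 0.842)² × SD² / 4².

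- Depression: 2 × 7.849 × 121 / 16 = 118.7, so 119 per group and 238 in total (stated 240). Power at 240 is 80.4%.
- Anxiety: 2 × 7.849 × 144 / 16 = 141.3, so 142 per group and 284 in total (stated 284). Power at 284 is 80.2%.

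The stated sizes therefore assume no gain from any covariate, and the planned 80% does not depend on baseline adjustment.

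**Step 2: add the baseline score.** Residual SD = SD × √(1 − r²), where r is the correlation between baseline and 6-month scores. The article gives no r; 0.3 to 0.7 is an assumed range. SE = residual SD × √(2/n), and power = Φ(4/SE − 1.96). The comparison row takes the strata as explaining none of the outcome variance.

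Anxiety trial, 142 per group:

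| r | Residual SD | SE | Power | Total N for 80% |
|---|---|---|---|---|
| none | 12.00 | 1.42 | 80.2% | 284 |
| 0.3 | 11.45 | 1.36 | 83.8% | 258 |
| 0.5 | 10.39 | 1.23 | 90.0% | 212 |
| 0.7 | 8.57 | 1.02 | 97.6% | 146 |

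Worked line for r = 0.5: 12 × √0.75 = 10.39; 10.39 × √(2/142) = 1.233; 4/1.233 − 1.96 = 1.28; Φ(1.28) = 0.90.

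**Step 3: depression trial, allowing for the severity stratum.** Suppose the stratum predicts the 6-month score only through baseline BDI-II, and correlates 0.5 to 0.7 with it (assumed). At r = 0.5 the stratum then correlates 0.5 × 0.5 = 0.25 to 0.5 × 0.7 = 0.35 with the outcome.

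- Strata only: residual SD 11 × √(1 − 0.25²) = 10.65 to 11 × √(1 − 0.35²) = 10.30; power 82.9% to 85.2%.
- With the baseline score: residual SD 11 × √0.75 = 9.53; power 90.2%.
- Gain: 90.2 − 85.2 = 5.0 to 90.2 − 82.9 = 7.3 points. Against a model with no covariates at all it would be 90.2 − 80.4 = 9.8.

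**Step 4: chance imbalance, anxiety trial.** Take the baseline SD as equal to the planning SD of 12 (an assumption; the article gives no baseline SD). The baseline difference between groups then has SE 12 × √(2/142) = 1.42. An imbalance of 1.96 SE, or 2.79 points, is exceeded in about 1 trial in 20. It moves the unadjusted 6-month difference by r × 2.79, which is 0.84 (r = 0.3), 1.40 (r = 0.5) or 1.95 (r = 0.7) points, against a target of 4.

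**The case against.** The strongest reply is that silence is not a decision. The adjustment sentence covers every analysis, including the exploratory logistic models, so it may be a common minimum rather than the full covariate list of the primary model. The name ANCOVA normally implies a continuous covariate, and baseline score is the obvious one. An article also condenses a fuller protocol, and a separate analysis plan may exist. This stands in part: a reader might infer that the plan rules out the baseline score, and the document does not say so. It does not dispose of the point, because the article itself states the model and the adjustment, and the phrase "analysis of variance (ANCOVA) will be used to examine differences between group means" gives two names for one method.

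Three further inferences are tempting and are not supported.

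- That the primary result would be biased or the type I error inflated. Under randomization neither follows, and the unadjusted confidence interval already allows for chance imbalance.
- That the trials would be underpowered. Step 1 shows that 240 and 284 reproduce without any covariate gain.
- That the hypotheses contradict each other. The sample size text speaks of whether "the collaborative care group and the consultation liaison group have improved similarly in terms of symptoms", while Statistical analyses refers to symptoms at 6 months. Under randomization the group difference in mean change and the group difference in 6-month means have the same expected value, so this is a difference of wording.

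**Conclusion.** The point holds as a matter of unclear specification and forgone precision. The only covariates named for the primary analysis are the stratification variables. The baseline score is available in both trials but is neither named nor excluded, and the method label does not settle the model.

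In the anxiety trial the literal model forgoes roughly 4 to 17 points of power for r between 0.3 and 0.7, with about 10 points at r = 0.5. In the depression trial the loss is about 5 to 7 points at r = 0.5. These sizes rest on the assumed r, on the assumed link between severity stratum and BDI-II, and, for the anxiety trial, on former treatment and disorder type explaining little of the 6-month score. If those two factors explain more, the anxiety gain is smaller too.

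If baseline adjustment was always intended, the change only records it. If it was not, the change improves the primary analysis in both trials.

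**What to change.** Before the allocation codes are opened, replace the model and adjustment sentences for continuous outcomes with wording of this kind: each continuous outcome measured at baseline is analysed by analysis of covariance on its 6-month score, with treatment, the stratification factors and the continuous baseline value of that outcome as covariates. Drop the words that call the method analysis of variance.

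By Table 2 this covers BDI-II, BAI, SDS, SCL-90-R and WHO-5, and the exploratory scales also collected at baseline. CSQ-8 and INSPIRE are collected only at follow-up and keep adjustment for the stratification factors alone.

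The cost is a sentence or two in the protocol or analysis plan. No new data, visits or participants are needed, and the stated sample sizes can stay as they are.

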## Discussion

The design of the trials has several strengths. The collaborative care model has been developed based on previous experiences and with special emphasis on meeting the needs of GPs. We hope this will increase the success of any subsequent implementation; fidelity reviews will be conducted to ensure faithfulness to the intervention; we recognize the risk of contamination of the control group when testing a system-level intervention, and therefore we compare the collaborative care group with a form of consultation liaison that equals the contaminating elements; the randomization is externally computer generated, which reduces the risk of selection bias; compared with the Collabri trials, the questionnaire battery has been shortened to enhance the follow-up rate; and the psychiatrist in the Collabri Flex team and many of the care managers and GPs also participated in the previous Collabri trials, and, accordingly, they have already worked within the framework of the similar Collabri model and have experienced being part of an RCT.

The design of the trials also has some limitations. Most outcomes, including the primary outcomes, are self-reported, which could lead to information bias and, possibly, overestimation of effects [74]; participants, the Collabri Flex team and GPs are not blinded to the allocation, which could lead to performance bias; because we compare two active intervention groups, it might be more difficult to detect a difference between groups than if we had compared collaborative care with treatment as usual; thus, accordingly, from these trials we will not be able to conclude whether collaborative care is more effective than treatment as usual. However, the results will supplement those of the cluster-randomized Collabri trials and together they will provide pivotal information about the effects of collaborative care in Denmark.

## Trial status

The Collabri Flex Trial for Depression and the Collabri Flex Trial for Anxiety were initiated in mid-January 2018. Recruitment is ongoing and expected to end 12 months after trial initiation. The results are expected after an additional 12 months. This protocol is version 2.

## Data Availability

Not applicable.

## Abbreviations

ASRS: Adult ADHD Self-report Scale
BAI: Beck Anxiety Inventory
BDI-II: Beck Depression Inventory II
CBT: Cognitive behavioral therapy
CDSMP: Chronic Disease Self-Management Program
CSQ-8: Client Satisfaction Questionnaire with eight questions
DREAM: Danish Register for Evaluation of Marginalization
EQ-5D-3 L: EuroQol five-dimension three-level version of health-related quality of life
GP: General practitioner
IPQ-R: Illness Perception Questionnaire Revised
MINI: Mini International Neuropsychiatric Interview
OPEN: Odense Patient data Explorative Network
SAPAS: Standardized Assessment of Personality: Abbreviated Scale
SCL-90-R: Symptom Checklist 90-Revised
SDS: Sheehan Disability Scale
WHO-5: World Health Organization-Five Well-being Index
